**Level one goals (all of the following)**

Heat rate within threshold range for age

Systolic blood pressure (BP) within threshold range for age

Capillary refill time <3secs

Oxygen saturations > 95% in room air

Table of the threshold heart rates, mean blood pressure and perfusion pressure (MAP-CVP) for age

| **Age (years)** | **Heart rate *(beats/min)** | **Systolic BP**  **(cm Hg)** | **Perfusion pressure (MAP-CVP)** |
| --- | --- | --- | --- |
| **Newborn** | 120–180 | 70 | 55 |
| **-1** | 120-180 | 75 | 60 |
| **-2** | 120-160 | 80 | 65 |
| **-7** | 100-140 | 85 | 65 |
| **-15** | 90-120 | 85 | 65 |

*should be only be assessed after the termination of a seizure

## Level two goals

CVP > 8 cm H20 or attainment of threshold perfusion pressure (see table)

plus urine output> 1mls/kg/hour.

**Randomisation procedure**

Randomisation will be conducted using a sealed card system. In the case of an emergency, where a child meets the clinical criteria for severe malaria but has evidence of profound shock (systolic blood pressure that is unrecordable or less < 80mm Hg) and volume resuscitation is required immediately, a children will be randomised before the receipt of the laboratory results and whilst consent is being obtained. The first 20mls/kg bolus will be given while the mother or guardian of the child is being consented and blood tests obtained.At this point if consent for the trial is refused or the malaria slide is negative for *P. falciparum* malaria parasites the child’s subsequent management will be as per local clinical protocol and by the attending clinicians’ judgement. The child will be dropped from the analysis of the study and the study number reallocated.

All children will be intensively monitored. The purpose of the intensive monitoring will be to establish the relative dose response and safety of each fluid regime required for correction of volume deficits and to monitor haemodynamic changes (in respiratory rate, oxygen saturation, heart rate, blood pressure and urine output) and clinical response induced by either colloid. To guide further management a central venous pressure line (CVP line) will be inserted into any child that develops refractory shock (failure to attain level one goals after one hour) or features suggestive of pulmonary oedema (development of bilateral fine, basal crepitations and falling oxygen saturations).

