## Pilot studies: We conducted a prospective phase I study examining the safety of volume expansion for children admitted with clinical features of severe malaria (impairedconsciousness or deep breathing) complicated by acidosis (base excess <-8). Patients recruited to the study underwent continuous monitoring of blood pressure, pulse rate, respiratory rate, oxygen saturation and central venous pressure using a multichannel recorder. Fifty-three children were recruited and all had evidence of compensated shock on admission, with tachycardia, tachypnoea and prolonged capillary refill time (≥3s). Mean central venous pressure (CVP) [standard error] at admission was low: 2.9 [0.5] cm water (see Figure); in the group with severe acidosis (base excess<-15) 44% had hypotension (systolic blood pressure < 80 mmHg). Improvements of haemodynamic indices and a reduction in acidosis followed administration of either saline or albumin. By 8 hours the mean CVP had increased to 7.5 [0.5] cm water (F=34.4, P<.001) and was associated with a reduction in mean respiratory rate 49 [2] to 41 [1], F=7.0, P=.009, reduced tachycardia 151 [5] to 141 [3], F=3.4; P=.06 and reduced capillary refill time. No child developed evidence of the life threatening complications of pulmonary oedema and raised intracranial pressure. We concluded that both albumin and saline were safe and that doses of between 20-40mls/kg given over the first hour after admission resulted in a correction of the features of hypovolaemia and resolution of the acidosis9.

Figure: Central Venous Pressure measurement in children with malarial acidosis: correction of hypovolaemia with volume replacement

Central venous pressure (CVP) measures the pressure in the column of blood returning to the heart (preload). In health, this is normally 5-8cm H2O. In sick children higher preloads ~ 8-10cm are often required. In these children with severe malaria complicated by acidosis CVP was low at admission (0 hours) and normalised following 20-40mls/kg intravenous bolus of 0.9% saline or 4.5% albumin (indicated by the diamond).

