##### c. Sampling

1. **Sample size determination**

These are pilot studies designed primarily to examine the safety of Gelofusin in children with severe malaria complicated by acidosis. As Phase I studies they are designed to provide adequate data to justify progression to next phase ie: multicentre studies, but with the desire to avoid exposure of a large group of children to a therapeutic intervention for which there is no available data in severe malaria. The trial will therefore, provide important data on the volumes required of Gelofusin in achieving satisfactory improvements in haemodynamic features of shock such in a similar manner to that which has been previously observed in children given albumin9. Formal sample sizes will therefore not be calculated. We aim to recruit 80 children: 40 will have moderate acidosis and 40 will have severe acidosis. 20 children in each group will receive Gelofusin and 20 will receive albumin. Since we showed that the greatest benefit of albumin was in those with coma24, at least 50% of the children recruited will have coma. Gelofusin, would be used in preference to albumin in larger studies if mortality were 10% (confidence interval 7.5-12.5%) or less.

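### Emergency-route children who receive study colloid and then have consent refused or a negative slide are dropped from the analysis of a safety trial, and their study number is reissued

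*Protocol*

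**What the plan says.** Sample size determination (Protocol, section 8c) gives the purpose: "These are pilot studies designed primarily to examine the safety of Gelofusin in children with severe malaria complicated by acidosis". The same section plans 80 children, 20 per colloid within each of two acidosis groups. It would carry Gelofusin into larger studies if mortality were 10% or less.

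Randomisation procedure (section 8) says: "Randomisation will be conducted using a sealed card system". It then describes an emergency route for a child who meets the clinical criteria for severe malaria, has an unrecordable systolic pressure or one below 80 mmHg, and needs volume at once. On that route "a children will be randomised before the receipt of the laboratory results and whilst consent is being obtained", and "The first 20mls/kg bolus will be given while the mother or guardian of the child is being consented and blood tests obtained".

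The exclusion applies "if consent for the trial is refused or the malaria slide is negative for" *P. falciparum*. Care then reverts to local practice, and: "The child will be dropped from the analysis of the study and the study number reallocated".

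No section of the protocol keeps these children in a safety set or says what happens to the opened card. Study Monitoring has the monitoring board review all deaths and life-threatening complications, without saying whether dropped children count.

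**The concern.** A child on this route has been randomised and has received study product before the decision to drop is taken. In a trial whose main question is whether Gelofusin is safe, that child's outcome is evidence on the question.

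The two grounds for dropping differ in kind:

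- **Negative slide.** Whether the child had malaria on admission was settled before any colloid was given. Leaving slide-negative children out of the efficacy comparison is defensible. Leaving them out of the safety record of a bolus they actually received is not.
- **Refused consent.** The family decides while the bolus is running or after it. No blinding is described, so refusal can follow from how the child is doing or from which colloid was hung. An exclusion of that kind can bias the comparison between arms.

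Reissuing the number is a separate defect of the enrolment procedure, which an analysis plan could not repair afterwards. It can disclose an allocation, or it can leave two treated children under one identifier.

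**Working it through.** **1. The plan's own figure.** 2 acidosis groups × 2 colloids × 20 children = 80, or 40 per colloid. This reproduces. The 10% rule therefore allows at most 0.10 × 40 = 4 deaths among 40 Gelofusin children.

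**2. How many children might use the route.** The pilot summary in section 4 reports that in the severe-acidosis group "44% had hypotension (systolic blood pressure < 80 mmHg", the same cut-off as the emergency trigger. Applied to the 40 severe-acidosis children planned here, 0.44 × 40 = 17.6, or 8.8 per colloid. This is an extrapolation, and probably a high one for that group, because the trigger also requires an immediate need for volume.

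**3. How many might be dropped.** The protocol gives no rate. Let f be the share of emergency entrants dropped and replaced until 17.6 are analysed. The extra exposed children number 17.6 × f/(1 − f), over both colloids:

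| Assumed f | Dropped, both colloids |
|---|---|
| 5% | 0.9 |
| 10% | 2.0 |
| 20% | 4.4 |
| 30% | 7.5 |

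About half of each figure would be on Gelofusin, so at f = 30% roughly 3.8. In the next table, 2 to 4 dropped Gelofusin children is thus the more plausible range, and 8 is a wide upper bound.

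**4. Effect on the 10% rule.** Suppose 4 of 40 retained Gelofusin children die: 10.0%, exact 95% interval 2.8-23.7%. With d dropped Gelofusin children and x deaths among them, mortality in all exposed is (4 + x)/(40 + d):

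| d | x = 0 | x = 1 |
|---|---|---|
| 2 | 4/42 = 9.5% | 5/42 = 11.9% |
| 4 | 4/44 = 9.1% | 5/44 = 11.4% |
| 8 | 4/48 = 8.3% | 5/48 = 10.4% |

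The rate exceeds 10% when 4 + x > 4 + 0.1d, that is when x > d/10. For any d below 10, one death is enough to cross the line, and with no deaths the rate falls.

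**5. Effect of reusing a number.** If the opened card goes with the number, k reuses make k of the 80 assignments known beforehand. With even odds on the rest, the expected share of correct guesses is (k + 0.5 × (80 − k))/80. For k = 2, 4 and 8 this is 51.3%, 52.5% and 55.0%, against 50%. If a fresh card is drawn, no allocation is disclosed, but one number then refers to two treated children.

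**The case against.** The strongest reply is that each ground has a reason. Section 11 requires informed consent, and the exclusion criteria give standard management only to children whose families decline. Use of a refuser's data therefore needs ethics approval. The safety question and the 10% rule concern children with severe malaria, so counting slide-negative deaths would change the population of that rule. Both points stand. They call for separate reporting and for approval of what may be used; they do not justify removing exposed children from the record.

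The monitoring board's review of all deaths could be read as covering dropped children. It may do so, but the text does not say it, and case review does not put them in a comparison by arm.

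It is also fair that the numbers are small. The 2.8-23.7% interval around 4/40 is far wider than any shift shown above.

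Several stronger readings are tempting, and the protocol does not support them:

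- *All emergency-route children are dropped, so the sickest are lost as a class.* Those with consent and a positive slide stay in.
- *Concealment is broken.* That holds only if the opened card travels with the number, which the text does not say.
- *Emergency children later found ineligible on base excess, haemoglobin or cerebrospinal fluid are kept.* The paragraph is silent on them, and silence is not a rule.
- *The emergency blood-pressure trigger contradicts the age table.* One is an entry trigger and the other a set of resuscitation goals, so the two may differ.
- *The rule makes Gelofusin look safer.* Two dropped children who both died would give 6/42 = 14.3% against 4/40, but that is one unfavourable corner of an assumed range.

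**Conclusion.** The point holds in this limited form. The protocol contains a stated rule that removes some randomised, colloid-treated children from the analysis of a trial designed primarily for safety, and reissues their study numbers. Only emergency-route children with refused consent or a negative slide are affected. Of the two exclusions, refusal is the one that can depend on response or colloid.

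The size cannot be fixed from the protocol. It depends on assumed drop rates, on deaths among the dropped, and on the pilot's 44% carrying over. Under those assumptions a few exposed children would disappear, and a Gelofusin result sitting exactly at 10.0% would become 10.4-11.9% with one death among 2 to 8 dropped, or 8.3-9.5% with none. The direction is unknown; what is shown is that the decision rule can turn on children the plan does not count. Disclosure of allocations is a conditional risk and modest in size (at most 55% correct guesses in the cases worked). The loss of a unique identifier is what follows otherwise.

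**What to change.** Replace the sentence on dropping and reallocation with: *A randomised number and card are never reused; a replacement child takes the next unused number and card. Every opened card is logged.*

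Then state how these children are reported:

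- Report safety and mortality by allocated arm in every child who received any study colloid, as far as consent and ethics approval allow. Show slide-negative children separately, so that the 10% rule can also be read in confirmed malaria.
- Where consent is refused, report the count by arm to the monitoring board and, if approved, vital status.
- Exclude slide-negative children from the efficacy analysis only, on the pre-treatment slide read without knowledge of arm.

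The cost is protocol wording, a few extra numbered cards, and ethics approval for the limited data on refusers. The downside is a small number of safety records from children without confirmed malaria. The change should be in place before enrolment, because records that were dropped and allocations that were disclosed cannot be recovered later.

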**Standard treatment of severe malaria**

All children with severe malaria are normally transferred to the high dependency unit. Standard management includes intravenous quinine infused in 5-10% dextrose, antibiotics (discontinued after negative blood cultures at 48 hours and normal lumbar puncture), antipyretics and anticonvulsants as per protocol. Hypoglycaemia is treated with a bolus of 2mls/kg of 25% dextrose. All children receive maintenance fluids (96mls/kg/day or 4mls/kg/hour of 5% dextrose/0.18% saline) but those with acidosis generally received intravenous volume expansion. Previous pilot studies have determined optimal volumes required. Children recruited into this study will receive only volume expansion by randomisation. At admission children will have blood taken for grouping and saved for cross-matching. Children with a haemoglobin < 5g/dl currently receive 20 mls/kg of whole blood.

# **d) Procedures**

Data collection and venous blood sampling will be in line with current, approved guidelines practiced on the KEMRI ward at Kilifi District Hospital. Details are listed below.

**i) Type of data to be collected and collection procedures to be followed.**

## Clinical procedures

The study will be conducted with continual monitoring of vital and neurological signs. Clinical assessment by members of the trial team will occur at 30 mins, 1 hour and followed by hourly (by the nursing personnel) until 8 hours post admission, and thereafter 4 hourly. One of the trial team will be attending to the child when they are receiving resuscitation fluids. Children will be managed according to the attainment of resuscitation goals described previously. The primary endpoints will be the correction of shock and volumes of colloid required to achieve this (ie: level one, level two etc).

**Potential complications**

The judicious use of intravenous fluids in children with a potential of raised intracranial pressure, cardiogenic shock or fluid overload is a concern. The study will be conducted with continual monitoring of vital and neurological signs. Further boluses of fluid will be withheld if vital and neurological signs indicate raised intracranial pressure (ICP) or heart failure. Raised ICP will be indicated by a rising blood pressure (>90% centile/age), together with a falling heart rate, the development of a sluggish reaction to or asymmetric pupillary reaction to light. Cardiac failure will be indicated by a worsening tachycardia and tachypnoea, de novo presence of fine crepitations in lung bases, deteriorating oxygen saturation and a sustained rise in CVP >15cm. These children will not receive any more fluid boluses and chest x-ray will be performed. Frusemide at 1mg/kg will be given to children in whom pulmonary oedema or right-sided heart failure is suspected or confirmed. In those with suspected raised ICP treatment with mannitol will be considered. The complications of a central venous pressure line include infection, blood loss and thrombosis. These will be minimised by using short CVP lines inserted into the femoral vein and advanced only 6-8 cm. They will remain in-situ for only up 48 hours then removed. The nurse in charge of the patient will only look after a maximum of two patients at one time.

**Study Monitoring**

A local data safety and monitoring board (DSMB) composed of clinical and scientifically qualified members will act as the main monitor for the trial, which will review all deaths life threatening complications ([name], [name] and [name]). These monitors will assess each death and children developing neurological sequelae on a case by case basis. Otherwise we intend to provide the DSMB summary data after the first 40 children have been recruited.

#### Blood sampling and Laboratory procedures

Blood count, venous blood gases, blood sugar and chemistry (sodium, potassium and calcium) plasma creatinine, albumin, osmolality and red cell rheology will be measured at admission and 24hrs. Clotting and will be assessed at admission, 8 hours after colloid infusion and at 24 hours after admission (the details of the coagulation tests are covered in a separate proposal entitled ‘Investigation of coagulation activation in children with severe malaria’). Additional measurements of venous gas, plasma sodium, potassium, calcium, creatinine, albumin, red cell rheology and blood sugar will be taken at 8 hours to assess the response to volume resuscitation. Blood volumes taken for the purposes of monitoring are to be kept well within the maximum locally agreed volumes. In total 5mls of blood will be taken at admission (including all the standard blood tests) and an additional 2.5 mls the following 24 hours.

**9. DATA MANAGEMENT**

**(a) Data storage**

Original paper based data would be kept on file for 5 years from the completion of the proposed study. Patient data stored on computers is confidential and access restricted. Clinical and other data are backed up daily and copies of data files stored both on site and in the KEMRI/Wellcome Trust computer centre in Nairobi.

**b) Provisions for data verification and validation.**

Currently all data is directly entered in File-Maker Pro where most variables entered have dichotomous values only and the values for numerical fields are selected from a list. Initial and final diagnoses are also chosen from a list of common diagnoses. The programmes have been written to include logical and range checks and flags for the reduction of duplication errors. Appropriate information quality control procedures are already established. Children fulfilling the admission criteria for the study will be flagged by the computer to alert the admitting physician.

Descriptive statistics will be used to compare the clinical characteristics of the groups at baseline (admission), 30minutes, 1 hr, 4 hrs, 8 hrs, 12 hrs and at 24 hours, by intervention. The major outcomes of interest will be the resolution of clinical features of shock and major side effects or complications; development of abnormal clotting indices, pulmonary oedema and death (as dependant variables) between the different interventions (independent variables). The primary measure of this outcome will compare the proportions attaining level one goals for resuscitation in those receiving albumin and Gelofusin. Using ANOVA baseline (admission) haemodynamic parameters (heart rate, respiratory rate, oxygen saturation, mean blood pressure and coma score) will compared to those at 1 hr, 2 hours and 8 hours between the different intervention groups. For the purpose of analysis percentage mean change in the parameter will be used between the baseline and next time point.

Expected outcome: We have shown that albumin results in low mortality (< 5%), whilst saline was associated with an overall mortality ~20%, rising to 46% in those with coma. Historical control data from children with the same clinical criteria show mortality was between 30-50%, when volume expansion was not routine. If the dose response to Gelofusin is similar to albumin then assessment of the clinical safety of Gelofusin will take the above mortality data into consideration, as well as the evidence arising from the coagulation studies.

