**Theoretical considerations for the use of colloid in severe malaria**

Most of in-vivo trials examining the effect of different colloids on haemostasis (usually measure by blood loss) have been conducted in clinically stable patient groups undergoing corrective orthopaedic or cardiac surgery. In septic shock coagulation and haemostasis is disordered. In severe malaria bleeding secondary to disseminated intravasular coagulation (DIC)3 and procoagulant activity has been reported in adults with severe malaria20,21. In children whilst DIC is rarely encountered, little to no information exists on the abnormalities in coagulation and homeostasis22. There are however, a number of considerations when considering the use of non-albumin colloids. Firstly, in severe malaria moderate degree of thrombocytopenia is invariable22. In children admitted with severe malaria to KDH, thrombocytopenia (platelets counts < 150x1012) is common (>55%)23. Dextrans and starches are known to reduce von Willebrand factor and increase the risk of bleeding18. In the presence of thrombocytopenia, a von Willebrand-like syndrome is a possible complication. Albumin has no effect on coagulation and the effects by gelatins are mild, usually related to a dilutional effect18.

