**6. NULL HYPOTHESES.**

1. There is no difference in the safety profile or effect on physiological parameters of shock using gelatin-based colloids and albumin for the correction hypovolaemia in children with severe malaria.
2. The use of either of the two colloids will lead to no changes in coagulation after administration.

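### Clotting is compared between arms as new-onset abnormality, which does not count worsening in a child already abnormal on that index, discards the size of any change, and does not match the protocol's own hypothesis of no change in coagulation

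*Protocol*

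**What the plan says.** Section 9b (the analysis text under data verification and validation) names the major outcomes to be compared between interventions. Besides resolution of shock, these include the "development of abnormal clotting indices, pulmonary oedema and death (as dependant variables"). The same section plans percentage change from baseline for the haemodynamic parameters (heart rate, respiratory rate, oxygen saturation, blood pressure and coma score). Clotting is not on that list.

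Elsewhere the coagulation question is about change. The second null hypothesis in section 6 reads "The use of either of the two colloids will lead to no changes in coagulation after administration". The third secondary aim in section 7 asks whether either colloid deranges coagulation. Section 5 promises serial measures, and its footnote says a linked proposal will allow changes after volume expansion to be described.

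The blood sampling section sets clotting samples at admission, 8 hours after infusion and 24 hours after admission. It lists the blood count separately and leaves the choice of coagulation tests to the linked proposal.

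On the state of children at entry, the theoretical considerations in the Background say that "in severe malaria moderate degree of thrombocytopenia is invariable", and that at the study hospital "thrombocytopenia (platelets counts < 150x1012) is common (>55" per cent). On coagulation itself they say: "In children whilst DIC is rarely encountered, little to no information exists on the abnormalities in coagulation and homeostasis".

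On size, section 8c states "We aim to recruit 80 children: 40 will have moderate acidosis and 40 will have severe acidosis", then "20 children in each group will receive Gelofusin and 20 will receive albumin", and adds "Formal sample sizes will therefore not be calculated".

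**The concern.** A child can develop an abnormality on an index only if that index was normal to begin with. If it was already abnormal at admission, further deterioration does not count towards the outcome as worded. In every child, a small and a large movement across the limit score the same, and a movement that stays on one side scores nothing. The outcome therefore answers a narrower question than the second null hypothesis, which covers change in any child.

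Coagulation is the particular safety question with a non-albumin colloid. Section 9b also makes the coagulation evidence an input to the judgement on Gelofusin's clinical safety. With 40 children per arm, an insensitive comparison will often show no difference, and that could be taken as reassurance when larger trials are planned.

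**Working it through.** **Inputs from the protocol.** Two acidosis groups × two arms × 20 = 80 children, so 40 per arm; the recruitment arithmetic is consistent. No alpha, power or effect is stated, so there is no power figure to reproduce. The only baseline haemostatic frequency is the platelet figure of more than 55%.

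**Assumptions.** Two-sided 5% level, the event rates and the size of shift below, the correlation between admission and later values, and every value of b (share abnormal at admission) other than 55%.

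**Step 1: who can have the event.** Children at risk per arm = 40 × (1 − b). At b = 55%, 40 × 0.45 = 18 per arm, so 36 of 80 can be scored and 44 cannot. At b = 30% it is 28 per arm, at 10% it is 36, and at 5% it is 38.

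**Step 2: effect of baseline abnormality on a yes/no comparison.** Take new abnormality of 10% v 40% in children normal at entry. Exact Fisher power with all 40 per arm at risk is 85%. The protocol does not say how a child abnormal at entry is scored, so three codings are shown:

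- excluded: n = 40(1 − b), 10% v 40%;
- counted as non-events: n = 40, 10%(1 − b) v 40%(1 − b), which is 4.5% v 18% at b = 55%;
- counted as events: n = 40, b + 10%(1 − b) v b + 40%(1 − b), which is 59.5% v 73% at b = 55%.

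| b | Excluded | Non-events | Events |
|---|---|---|---|
| 5% | 83% | 82% | 76% |
| 10% | 80% | 79% | 66% |
| 30% | 66% | 64% | 40% |
| 55% | 43% | 35% | 18% |

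The loss is large at 55%. At 5–10% it is small under the first two codings.

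**Step 3: yes/no outcome against the measured value.** Admission and later values are taken as bivariate normal with correlation r. Every Gelofusin child is worsened by 0.5 SD, the limit is set so that a share b is abnormal at admission, and there are 40 per arm (4,000 simulated trials per row).

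| r | b | Excluded | Non-events | Events | ANCOVA |
|---|---|---|---|---|---|
| 0.5 | 10% | 20% | 17% | 13% | 72% |
| 0.5 | 30% | 27% | 23% | 17% | 73% |
| 0.5 | 55% | 19% | 12% | 12% | 72% |
| 0.7 | 10% | 20% | 15% | 12% | 88% |
| 0.7 | 30% | 29% | 24% | 17% | 86% |
| 0.7 | 55% | 24% | 16% | 13% | 87% |

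Hand check of the ANCOVA column: the standard error of the adjusted difference is √[2(1 − r²)/40]. At r = 0.7 this is √(1.02/40) = 0.160, so 0.5/0.160 = 3.13 and power is about Φ(3.13 − 1.96) = 88%. At r = 0.5 it is √(1.5/40) = 0.194, giving 2.58 and about Φ(0.62) = 73%.

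**Step 4: where the gap comes from.** In the same simulation, a yes/no comparison of abnormality after infusion that ignores admission status has 22–34% power. At r = 0.7 and b = 55% it has 32%, against 13–24% for the new-onset codings and 87% for ANCOVA. Restricting to new onset therefore costs 8 to 19 points there (32 − 24 and 32 − 13). The other 55 points (87 − 32) come from cutting the value in two and not using the admission value. Consistent with this, the new-onset codings do no better at b = 10% than at 55% in any systematic way.

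**The case against.** A reader might infer that a large share of the children cannot be scored, that worsening in them goes unseen, and that the trial is tilted towards finding no harm. The documents do not support that reading, for three reasons.

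- The 55% is a platelet figure. The blood count is listed apart from clotting, and the tests are left to a proposal that is not shown. For coagulation in children the protocol says almost nothing is known and DIC is rare. The indices are also plural, so a child abnormal on one could become abnormal on another.
- Worsening is not invisible. Serial values are taken, the linked proposal is to describe changes, and the safety judgement draws on the coagulation studies as a whole. Only the yes/no comparison misses it.
- Cut-offs and the scoring of children abnormal at entry may properly sit in an analysis plan or in the linked proposal. Their absence is not an error.

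It can also be said that this is a pilot with no formal sample size and that the Summary places coagulation among secondary endpoints, so no promised power is missed. It is fair, too, that the advantage of the measured value in step 3 is mostly the general cost of dichotomising.

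All of this limits the size of the point. It does not remove it. Section 9b positively names a new-onset outcome for the comparison between arms. That differs from the change named in the second null hypothesis, and the values needed for the better comparison are already collected.

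**Conclusion.** The point holds as a mismatch between outcome and hypothesis, with a clearly better analysis available. As worded, the clotting comparison does not count worsening in a child already abnormal on that index, discards the size of change, and does not match the second null hypothesis or the third secondary aim.

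How many children are affected is unknown. It is more than 55% only if platelet count is an index; otherwise the protocol gives no rate. Under the assumed 0.5 SD shift, 40 per arm and r of 0.5 to 0.7, power is roughly 12–30% for the new-onset codings and about 72–87% for the adjusted comparison. The contrast hardly depends on the 55% and is mainly due to dichotomising. These figures rest on assumed normality, shift and correlation. They illustrate the loss and do not predict this trial's result. The change is worth making, but the point does not undermine the trial.

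**What to change.** In section 9b, replace the clotting comparison with this: each clotting index is compared between arms as its post-infusion value (log scale if skewed) by ANCOVA with the admission value as covariate, in all children with samples. State which of the 8-hour and 24-hour values is the main one.

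Keep new abnormality as a descriptive result, with its denominator limited to children normal on that index at admission. Tabulate worsening among those already abnormal.

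The cost is wording only, because the admission, 8-hour and 24-hour samples are already planned; no further blood or children are needed. The downside is that a mean difference (or a ratio, on the log scale) is slightly harder to read than a percentage, which the descriptive table offsets. Children who die before the later sample have no value to compare, so the number sampled should be shown by arm beside the deaths.
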